## Abstract

**Background::**

Colorectal carcinoma has a high incidence rate and the high mortality rate has always been an important global health challenge. Surgical treatment is widely performed in patients with colorectal carcinoma. Fast track surgery (FTS) applies evidence-based medical concept to optimize the management during the operation, so as to reduce the psychological and physical trauma stress of surgical patients and make them recover rapidly. We perform this protocol for randomized controlled study to evaluate the efficacy of a rapid rehabilitation care in colorectal carcinoma surgery.

**Methods::**

It is a single-center randomized controlled study to be conducted from January 2021 to December 2021. It was authorized via the Ethics Committee of the Huzhou Central Hospital (20191127-01). Eighty participants who undergo colorectal carcinoma surgery will be included in this research. Patients are randomly assigned to control group (standard management group, including 40 samples) and study group (the FTS group, including 40 samples). The main results are times of postoperative exhaust, first defecation, ambulation, first eating, and postoperative hospital stay. Secondary outcomes are incidence of nausea and emesis, wound infection, urinary tract infection, lung infection, deep vein thrombosis, and rehospitalization rate among the 2 groups. All analyses are conducted using the SPSS for Windows Release 15.0.

**Results::**

Figure 1 shows the clinical results between groups.

**Conclusion::**

The research can offer a reliable basis for the effectiveness of a rapid recovery nursing program in patients with colorectal carcinoma.

**Trial registration::**

This study protocol was registered in Research Registry (researchregistry6038)

## Introduction

1

Colorectal carcinoma has a high incidence rate and the high mortality rate has always been an important global health challenge.^[1,2]^ About 10% of deaths occur annually in colorectal carcinoma, and the incidence rate and mortality rate of men is one-fourth higher than that of women.^[3]^ The incidence rate varies in different geographical locations, and is often higher in most developed countries. With the rapid progress of developing countries, it is estimated that there will be 2.5 million colorectal carcinoma patients in the world by 2035.^[4]^ However, in highly developed countries, the incidence of colorectal carcinoma is becoming stable and decreasing. This is mainly due to the increase of colorectal carcinoma related screening programs and colonoscopy in developed countries, as well as lifestyle and diet management.^[5]^ Although genetic factors, obesity, lifestyle, and living environment are associated with the disease, the specific relationship is not yet fully clear.

Surgical treatment is widely performed in patients with colorectal carcinoma.^[6]^ However, several patients are associated with several postoperative complications, which delays recovery. Fast track surgery (FTS) applies evidence-based medical concept to optimize the management during the operation, so as to reduce the psychological and physical trauma stress of surgical patients and make them recover rapidly.^[7,8]^ Auxiliary nursing is an important procedure in the treatment of carcinoma, which is used to meet the physical and mental needs, social needs, information acquisition, and actual needs of patients.^[9]^ The concept of continuous care during surgery has been successfully accepted in surgery.^[10]^ Li et al^[11]^ reported that FTS nursing program can efficaciously relieve the bad mood and pain of patients with hip fracture. Currently, few studies have investigated the clinical effect of FTS in perioperative nursing of colorectal carcinoma surgery. We perform this protocol for randomized controlled study to evaluate the efficacy of a rapid rehabilitation care in colorectal carcinoma surgery.

## Materials and methods

2

### Study design

2.1

It is a single-center randomized controlled study to be conducted from January 2021 to December 2021. This study is performed according to the SPIRIT Checklist of randomized researches. It was admitted via the Ethics Committee of the Huzhou Central Hospital (20191127-01), and it has been registered in the research registry (researchregistry 6038).

### Inclusion and exclusion criteria

2.2

Inclusion criteria included colorectal carcinoma testified by pathology; and patients willing to participate in the survey and finish the chart independently. Exclusion criteria included patients with psychiatric history; patients taking psychotropic drugs within the last 6 months; patients with palliative gastrectomy; and patients with other severe visceral diseases.

### Subjects

2.3

Eighty participants who undergo colorectal carcinoma surgery will be included in this research. In the random envelope, a random number is assigned to whole patients through the random-number table, and the distribution result is invisible. Patients are assigned randomly to control group (standard management group, including 40 samples) and study group (the FTS group, including 40 samples).

### Intervention

2.4

#### Study group

2.4.1

Preoperative preparation. The medical personnel explains common sense in nursing, first-aid steps, and how to act in concert with medical personnel during perioperative period. Before surgery, the staff builds a trusting relationship with patients to enhance their obedience, and provides psychological consulting to help patients deal with preoperative anxiety and fear of surgery.

Intraoperative steps. Short effect general anesthesia and short effect regional block anesthesia are used in the operation. During the operation, the fluid should be strictly regulated, and the patient's normal temperature should be maintained with a heater to prevent heart overload, water intoxication, cell swelling, and other complications.

Postoperative care. Nonsteroidal anti-inflammatory drugs (NSAIDs) and self-control analgesia are given after operation. The first day after operation, the patients are in bed for 4 hours. Low power red laser is applied to irradiate the surgical area to promote the wound healing. Antibiotics are used on the first day after operation, and the bladder balloon is dislodged the following day.

#### Control group

2.4.2

Preoperative preparation. Patients take cathartic orally and receive clean enema.

Intraoperative steps. A nasogastric tube is inserted until the passage of gas by anus, and general anesthetics are during the operation.

Postoperative care. After surgery, dolantin, morphine, and other opioid agents are used for analgesia. Before normal eating, intravenous injection of nutrient solution is used as nutritional supplement, and antibiotics are stopped after the blood picture and body temperature return to normal level.

### Outcomes

2.5

The main results are times of postoperative exhaust, first defecation, ambulation, first eating, and postoperative hospital stay. Secondary outcomes are incidence of nausea and emesis, wound infection, urinary tract infection, lung infection, deep vein thrombosis, and readmission rate between the 2 groups.

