### Statistical analysis

2.6

All analyses are conducted using the SPSS for Windows Release 15.0. All results are expressed with appropriate form, for instance, mean, median, standard deviation, and percentage. The comparison between the 2 groups is conducted through applying the independent samples *t* test or the Mann–Whitney *U* test. And for the contrast of categorical variables between the groups, it can be implemented with Chi-square test. The *P* < .05 means that the results are statistically significant.

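### Five unranked main outcomes, each judged at P < .05, leave the error rate behind the single effectiveness conclusion above 5% if any one of them counts as success

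*Protocol article*

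**What the plan says.** Section 2.5 (Outcomes) of the protocol article lists five primary endpoints on an equal footing: "The main results are times of postoperative exhaust, first defecation, ambulation, first eating, and postoperative hospital stay". The Methods part of the abstract gives the same five, also unranked. Section 2.5 then lists six further endpoints: "Secondary outcomes are incidence of nausea and emesis, wound infection, urinary tract infection, lung infection, deep vein thrombosis, and readmission rate between the 2 groups".

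Section 2.6 (Statistical analysis) gives the test for continuous outcomes: "The comparison between the 2 groups is conducted through applying the independent samples" *t* test or the Mann–Whitney *U* test. It sets one threshold for everything: P "< .05 means that the results are statistically significant". It gives no testing order, no adjusted threshold and no rule for how many of the five must be positive.

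The sample is fixed in section 2.3: "Eighty participants who undergo colorectal carcinoma surgery will be included in this research", 40 in each arm. Section 5 (Conclusion) treats the trial as answering a single question, whether the programme works in these patients.

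**The concern.** Five tests feed one conclusion, and nothing says how they combine. A threshold of .05 controls the error of one test. It does not control the error of a conclusion that may rest on whichever of five tests came out best. With no primary outcome named in advance, the most favourable main result can be presented as the finding, and a reader cannot treat it as a 5%-level result. In a trial of 80 patients, which section 4 itself calls relatively small, chance differences on single outcomes are a practical risk.

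**Working it through.** **Inputs from the article.** Five main outcomes (2.5); threshold .05 for each (2.6); 40 per arm (2.3).

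**Inputs not in the article, so assumed.** Tests are two-sided; success means at least one of the five is significant; the five test statistics are normal with a common correlation ρ, varied from 0 to 0.9. The article states no familywise error rate and no sample-size derivation, so it has no figure of its own to reproduce.

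**Step 1: independent outcomes.** The chance of at least one P < .05 under no effect is 1 − 0.95^5 = 1 − 0.774 = 0.226.

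**Step 2: correlated outcomes.** With c = 1.96, the chance is

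1 − ∫ φ(u) [Φ((c − √ρ·u)/√(1−ρ)) − Φ((−c − √ρ·u)/√(1−ρ))]^5 du.

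**Step 3: false results in favour of FTS only.** Each test contributes 2.5%. At ρ = 0 the chance is 1 − 0.975^5 = 1 − 0.881 = 0.119. For other ρ the integral is the same with the lower-tail term removed.

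| ρ (assumed) | At least one false positive, either direction | At least one false positive favouring FTS |
|---|---|---|
| 0 | 22.6% | 11.9% |
| 0.3 | 20.9% | 10.5% |
| 0.5 | 18.3% | 9.1% |
| 0.7 | 14.8% | 7.4% |
| 0.9 | 10.2% | 5.1% |
| *One test alone* | *5%* | *2.5%* |

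The two-sided figure falls to 18% at ρ of about 0.52 and is lower beyond that.

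**Step 4: check by simulation.** Two-sample *t* tests with 40 per arm (20,000 runs per setting) gave 22.4%, 21.0%, 18.6% and 14.5% at ρ = 0, 0.3, 0.5 and 0.7, in line with the integral.

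**Step 5: if all five had to be significant.** In the same simulation this happened in 0%, 0%, 0.08% and 0.5% of runs. Under that rule there is no inflation.

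**Step 6: what an adjustment does.** With the smallest P tested at .05/5 = .01, familywise error under no effect is 1 − 0.99^5 = 4.9% if the outcomes are independent, and 4.2% at ρ = 0.5.

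**Step 7: what an adjustment costs.** By the normal approximation, the difference detectable at 80% power with 40 per arm is (1.960 + 0.842) × √(2/40) = 0.63 SD at .05 and (2.576 + 0.842) × √(2/40) = 0.76 SD at .01. With the *t* distribution these become 0.634 and 0.781 SD.

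**The case against.** The strongest reply is that the article never says one positive outcome is enough. Section 2.6 only says when a result is significant. If each outcome is reported as its own claim, each test keeps its 5%; if all five must succeed, nothing is inflated. This stands, and it makes every figure above conditional. It does not remove the defect, because section 5 draws one overall conclusion and the article requires nothing stricter than a single positive result.

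Two stronger readings are tempting, and the document supports neither.

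- A reader might infer that the chance of a false claim of efficacy is about 18-23%. That range holds only for correlations up to about 0.5. The five outcomes are linked recovery times in the same patient, so higher values are plausible. The range also counts results showing FTS to be worse, which are not efficacy claims; in favour of FTS alone the figure is about half as large.
- A reader might add the six secondary tests to the count. They are already labelled secondary. They are comparisons of incidences with 40 per arm, where a chi-square test of a rare event can reject well below 5% of the time, and independence among related complications is unlikely. They do not belong in this error rate.

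It can also be said that a separate analysis plan, not shown, may contain a multiplicity procedure. That is possible, so the mere absence of a procedure here is not the point. The article itself fixes five co-equal main outcomes and a flat threshold, and an adjustment made elsewhere would change the rule stated in 2.6. Finally, section 4 asks for larger studies to confirm the results. That tempers the claim only partly, since section 5 still calls the basis reliable.

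**Conclusion.** The point holds in conditional form. If any one of the five main outcomes counts as success, the two-sided chance of at least one false-positive main result is between about 10% and 23%, two to four and a half times the nominal 5%. The chance of one favouring FTS is between about 5% and 12%, roughly two to five times the 2.5% of a single test. Where the true value lies depends on the correlation among the outcomes, which the article does not give. The size also rests on two-sided tests and on the inferred any-one-of-five rule. That inflation exists under this rule does not depend on the choice of correlation: it is about twofold even at 0.9.

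**What to change.** Either of two changes is enough.

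1. **One primary outcome.** In 2.5, name one of the five as primary, tested at P < .05, and move the other four to secondary. This restores 5% and costs no power for the chosen outcome. The price is that the other four can no longer support a confirmatory claim.
2. **Keep all five under Holm.** In 2.6, compare the smallest P with .01, the next with .0125, then .0167, .025 and .05, stopping at the first failure. State that efficacy is claimed only for outcomes that survive. The first step then needs a larger effect: the difference detectable at 80% power with 40 per arm rises from 0.63 to 0.78 SD. Put another way, power at 0.63 SD falls from 80% to about 59% at that step (normal approximation).

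Under either option, state that the six existing secondary outcomes are supportive, and repeat the choice in the abstract. The edit is about two sentences in 2.5 and 2.6, made before outcomes are compared between arms, with no change to recruitment, treatment or data collection. If a separate analysis plan already contains such a rule, 2.6 should be brought into line with it.

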### Statistical analysis

2.6

All analyses are conducted using the SPSS for Windows Release 15.0. All results are expressed with appropriate form, for instance, mean, median, standard deviation, and percentage. The comparison between the 2 groups is conducted through applying the independent samples *t* test or the Mann–Whitney *U* test. And for the contrast of categorical variables between the groups, it can be implemented with Chi-square test. The *P* < .05 means that the results are statistically significant.

## Results

3

Figure 1 shows the clinical results between groups.

**Figure 1 F1:**
[figure not shown]
The clinical results between groups.

## Discussion

4

As a new surgical nursing pattern, FTS is broadly adopted in gynecology, orthopedics, and general surgery.^[12–14]^ It refers to the cooperation of nurses, anesthesiologists, specialists, patients’ families, nutritionists, and rehabilitation therapists to minimize the stress reaction during the operation, promote the postoperative recovery, and lower the hospitalization time and costs.^[15]^ Its concept is quite different from the former concept, which greatly impacts and changes the existing surgical treatment methods.^[16]^ For colorectal carcinoma surgery, the conventional concept emphasizes the need of routine preoperative bowel preparation, such as enema cleaning.^[17]^ Recent studies have found that excessive bowel preparation can cause intestinal flora imbalance and injure the intestinal natural barrier, thus increasing the probability of postoperative abdominal infection. At the same time, long-term fasting of water and food will cause the dehydration, resulting in water and electrolyte balance disorder, which is not beneficial to postoperative recovery and improvement of nutritional status. This is the first randomized controlled study to assess the efficacy of a rapid rehabilitation care in colorectal carcinoma surgery. However, the sample size we used is relatively small. In order to confirm the results, the larger investigations are required.

## Conclusion

5

The research can offer a reliable basis for the effectiveness of a rapid recovery nursing program in patients with colorectal carcinoma.
